#### Experimental group

2.6.1

The participants in the experimental group will receive standard care along with QSHTD (two 7.4 g packets, taken orally twice daily after meals) for a duration of 12 weeks, and the entire observation and follow-up period will span 24 weeks.

#### Control group

2.6.2

The control group participants will receive standard care along with placebo granules (two 7.4 g packets, taken orally twice daily after meals) for a duration of 12 weeks. The entire observation and follow-up period will span 24 weeks.

#### Concomitant medication during the trial

2.6.3

(1)Use of any other traditional Chinese patent medicines or decoctions will be prohibited during the test.(2)Any patients entering the screening period must discontinue the usage of any long-acting nitrate drugs (such as long-acting nitroglycerin) or any other anti-angina treatments. However, they may continue using a beta-blocker and/or calcium channel blocker if they are taking one.(3)Throughout the study period, patients will be prohibited from adding or using any of the following medications, in addition to maintaining their original medication: beta blockers, calcium antagonists, nitrate drugs (except for the use of short-acting nitroglycerin for angina attacks).(4)Any medications or treatments necessary for managing coexisting conditions should be documented, including the drug name (or other treatment name), dosage, frequency of use, and duration. This data is crucial for both analysis and reporting.

### Outcome measurements

2.7

#### Primary outcomes

2.7.1

The main endpoint is the change in myocardial blood flow (MBF), assessed through adenosine stress RTMPE, following a 12-week treatment period.

#### Secondary outcomes

2.7.2

(1) Canadian Cardiovascular Society Classification (24); (2) Seattle Angina Questionnaire (24); (3) TCM symptom evaluation; (4) MACE incidence rate, including all-cause mortality, nonfatal myocardial infarction, stroke, target vessel revascularization and stent thrombosis events.

Table 2 delineates the precise collection times for the outcome measures.

### Safety assessment

2.8

Our team will meticulously document the exact timing, intensity, duration, interventions applied, and potential outcomes of all adverse incidents. For each documented incident, the investigator will also assess the connection between the adverse events and the medications under study. In line with ICH guidelines, SAEs will be classified as any occurrences that could lead to hospitalization, inability to work, birth defects, or fatalities (25). The investigator will notify the ethics committee of any SAE in 24 h.

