#### Inclusion criteria

2.2.4

(1)Age range is from 18 to 80 years old.(2)PCI performed within the previous 2 years and rSS ≥ 2 points; or PCI was performed at least 2 years before and coronary angiography was performed within the previous 2 years with rSS ≥ 2 points; or PCI was performed at least 2 years before and there is untreated or unsuccessfully treated chronic total occlusion.(3)Meet the 2017 clinical diagnostic criteria for phlegm-damp syndrome in CHD, as well as the dampness syndrome diagnostic criteria.(4)Agree to undergo adenosine stress real-time myocardial perfusion echocardiography (RTMPE).(5)A signed consent form is required.

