### Recruitment process

2.3

The research will include participants from both the outpatient and inpatient departments of the Guangdong Provincial Hospital of Traditional Chinese Medicine. Subjects who meet the eligibility criteria and provide informed consent will advance to a screening phase, while those who do not fulfill these requirements will be excluded prior to randomization. Principal investigators and attending physicians will jointly conduct eligibility assessment for enrolled participants based on specific inclusion/exclusion criteria. Registered participants will then be allocated through an online system for intervention and follow-up phases of the experiment. Ineligible individuals' demographic data, as well as any reasons for non-participation, will also be documented alongside strict confidentiality measures.

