### Blinding

2.5

This trial will be conducted in a double-blind manner, ensuring that neither the participants nor the research staff are aware of the group assignments. The Jiangyin Tianjiang Pharmaceutical Co., Ltd. (Jiangyin, China) will produce both the QSHTD and the placebo granules. The placebo will be designed to closely resemble the QSHTD in all aspects, such as color and flavor. All medications will adhere to the standards set by the National Drug Manufacturing Code of China. The blinding process and the maintenance of the blind will be handled by the TCM Clinical Research Methodology Team at Guangdong Provincial Hospital of Traditional Chinese Medicine. An emergency letter for each drug code will be created during the randomization and blinding process, and it will be securely sealed according to the corresponding drug group. If a serious adverse event (SAE) occurs or if urgent medical care is required, the principal investigator can use the online randomization system to request unblinding. When unblinding becomes inevitable, the participant will be excluded from the study, and the investigator must inform the examiner of the cause within 24 h. If unblinding is essential, the individual will be removed from the research, and the investigator must convey the reasons to the examiner within a 24-hour period.

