### Data analysis and managament

2.10

Data analysis will be performed using SAS 9.2 (SAS Institute Inc., USA) according to a pre-established statistical plan. The evaluation of effectiveness will adhere to the intention-to-treat principle. Quantitative data will be analyzed using methods such as ANOVA. Categorical data will be evaluated with chi-square tests and Fisher's exact test, while non-parametric rank sum tests and CMH chi-square tests will be used for ordinal data. The significance level will be set at *α* = 0.05, and a *P*-value below 0.05 will indicate a statistically significant difference. Descriptive statistics will summarize the baseline characteristics of the two groups. For continuous variables that are normally distributed or have an unknown distribution, *T*-tests or Mann–Whitney *U*-tests will be employed. To address missing data, appropriate imputation strategies will be used to minimize potential bias. This will involve multiple imputation techniques, allowing us to create several complete datasets by estimating missing values based on observed data trends. Proper handling of data is crucial for maintaining the precision, reliability, and traceability of clinical trial information, as stipulated by the Technical Guidelines for Clinical Trial Data Management (27) and the Good Clinical Practice standards (28).

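### Section 2.8 defines a serious adverse event by what it might lead to, so ordinary angina can qualify and the AE/SAE split rests on conjecture (minor wording correction)

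*Protocol article*

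**What the plan says.** Section 2.8 (Safety assessment) refers to ICH guidelines and then gives its own test of seriousness: "SAEs will be classified as any occurrences that could lead to hospitalization, inability to work, birth defects, or fatalities". It attaches a duty to the label: "The investigator will notify the ethics committee of any SAE in 24 h".

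Other sections bear on how the test works in practice:

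- Section 2.3 on recruitment: "The research will include participants from both the outpatient and inpatient departments" of the hospital.
- Section 2.2.4, first inclusion criterion: "Age range is from 18 to 80 years old". The second criterion requires a residual SYNTAX score of at least 2, or a chronic total occlusion that is untreated or was treated without success.
- Section 2.6.3 restricts anti-anginal drugs during the study, "except for the use of short-acting nitroglycerin for angina attacks".
- Table 2 lists AEs and SAEs on separate rows at every visit.
- Section 2.5 on blinding: "If a serious adverse event (SAE) occurs or if urgent medical care is required, the principal investigator can use the online randomization system to request" (what is requested is that the code be broken). It goes on: "When unblinding becomes inevitable, the participant will be excluded from the study". A near-duplicate sentence then describes unblinding that is *essential*.

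**The concern.** A definition of seriousness has to let two people looking at the same event reach the same classification. A test of what happened (was the patient admitted, did the patient die) usually does. A test of what might have happened does not, because it asks the investigator to imagine a course that the event did not take.

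This matters more here than in many trials because the expected symptom of the disease is itself an event that can end in admission. If the wording is applied as written, a routine angina attack can be entered as an AE for one patient and as an SAE for another. The SAE table would then partly reflect classification habits, and the 24 h notices to the ethics committee could include episodes that were never serious in fact.

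The list of outcomes raises a second, smaller question. Two kinds of event that this population can have, a lengthened stay in someone already in hospital and disability in someone who does not work, are not named. Whether they count depends on how broadly the reader takes the rest of the sentence.

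**Working it through.** No arithmetic applies, because the definition rests on no sample size, rate or threshold. The check is to apply the sentence to cases that the article itself foresees.

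**Case 1: an angina attack relieved by short-acting nitroglycerin, with no admission.** Such attacks are foreseen in 2.6.3. Under 2.2.4 the patient has residual disease by residual SYNTAX score or an occlusion not successfully treated.

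- Test as written (potential): in such a patient the attack could plausibly have ended in admission. It can be classed as an SAE, and notification within 24 h follows.
- Test by actual outcome: there was no admission, death or disability. It is an AE.

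The two tests give different answers for an event that the plan expects. Nothing else in 2.8 supplies an actual-outcome test. The sentence on documentation also speaks of the potential outcomes of adverse incidents.

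**Case 2: an adverse event in a participant already in hospital that lengthens the stay.** Section 2.3 makes inpatients eligible. The four listed outcomes are hospitalization, inability to work, birth defects and fatalities.

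- Strict reading: the event led to no new hospitalization, and no listed outcome clearly applies.
- Broad reading: an event bad enough to lengthen a stay is one that could have led to hospitalization, so it qualifies.

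**Case 3: lasting functional loss in a retired participant.** Section 2.2.4 admits patients up to age 80.

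- Strict reading: inability to work has no clear meaning for someone who does not work.
- Broad reading: the phrase means loss of capacity whatever the employment status, or the event could have led to admission, so it qualifies.

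In all three cases the classification turns on how the reader takes the sentence. Table 2 needs a single answer, because AEs and SAEs are separate rows.

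**The link to unblinding.** Within 2.5, the first sentence on the subject lets the principal investigator request the code when an SAE occurs or when urgent care is required. Urgent care is thus a separate ground, and the SAE label stands as a ground by itself. The next two sentences treat unblinding as something that happens when it is *inevitable* or *essential*. The section does not say whether those words limit the request or only describe what follows it. With the wide definition in 2.8, a nitroglycerin-relieved angina attack would meet the first sentence and plainly not the later two.

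**The case against.** The strongest reply is that this is a journal article. The sentence opens by invoking ICH guidelines and cites a source, and the full protocol, SAE form and operating procedures are not shown. It may be a loose paraphrase of a sound definition. That is fair, and it lowers the weight of the point. Whether the wording departs from the cited guideline cannot be checked here, and nothing above relies on it. The reply does not remove the point, because the article does not leave the definition to another document. It states an operative test, and that test does not give a workable AE/SAE split.

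A reader might go further in four directions. The document does not support them.

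- *That prolonged stays and disability in retired patients are excluded.* They are unlisted, not excluded, and the wide wording would often catch them. The text cannot be called both too wide and firmly too narrow. What can be said is that it is unclear.
- *That the SAE label opens the code.* It permits a request, which is discretionary, and the surrounding text speaks of *inevitable* or *essential* unblinding. No one is unblinded by the label. Exclusion of an unblinded participant sits uneasily with the statement in 2.10 that "The evaluation of effectiveness will adhere to the intention-to-treat principle", but that tension exists however an SAE is defined.
- *That real safety signals would be lost.* Section 2.8 has timing, intensity, duration, interventions and relation to study drug recorded for every adverse event. Section 2.7.2 counts death, nonfatal infarction, stroke, target vessel revascularization and stent thrombosis as actual events.
- *That the comparison between arms is biased.* Investigators are blinded, so loose classification should fall largely equally on both groups. The harm is noise and poor reproducibility. No bias has been shown.

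**Conclusion.** The point holds as a minor wording defect. Section 2.8 fixes seriousness by potential outcome. In a population whose angina attacks are foreseen, this literally admits ordinary angina as an SAE and makes the AE/SAE split in Table 2 a matter of conjecture. Prolongation of an existing stay and disability not tied to work are left unstated. Section 2.5 uses the same label as a ground for an unblinding request without saying how its own limiting words apply.

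No numerical size can be given. It is tempting to assume that 5 to 10% of the 98 patients have an actual hospitalization or death and that 20 to 50% have an episode that could have led to admission. That gives 98 × 0.20 / (98 × 0.10) = 2 at one end and 98 × 0.50 / (98 × 0.05) = 10 at the other. Neither range has any anchor in the document, and the ratio only restates the assumptions. It also presumes that investigators would report nitroglycerin-relieved attacks as serious. It should not be cited as the size of the problem.

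The conclusion assumes that the sentence in 2.8 is the definition investigators apply. If the full protocol or SAE form already classifies by actual outcome, only the article's sentence needs correcting. The primary endpoint is not affected.

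**What to change.** In 2.8:

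- Classify by the actual outcome of the event, so that it must *result in* a listed outcome and not merely be capable of it.
- Name prolongation of an existing hospitalization alongside hospitalization.
- Replace the work-based item with disability or incapacity regardless of employment.

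In 2.5, reconcile the sentence that lets an SAE support an unblinding request with the later sentences that speak of *inevitable* and *essential* unblinding. The text should make clear that the SAE label alone is not a ground for a request. Merging the two near-duplicate sentences on exclusion and 24-hour reporting would help.

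The cost is small: a wording amendment, which 2.11 requires to go to the ethics committee before use, an updated SAE form and brief retraining of investigators. Any events already classified under the present wording would have to be re-read once against the new one.

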### Sample size calculation

2.9

The sample size calculation will be based on the mean and standard deviation of the variation in MBF. According to the literature, the MBF variation in a conventional treatment group increased by 0.52 ± 0.72 (dB/s) after 12 weeks, while in the conventional combined TCM treatment group, MBF variation increased by 0.97 ± 0.68 (dB/s) after 12 weeks (26). After substituting the above values into PASS11 software with *α* = 0.05 and *β* = 0.20, the sample size required for each group was determined to be 39 cases. Accounting for a 20% dropout rate, this was adjusted to 49 cases per group. The two groups required a total of 98 patients.

### Data analysis and managament

2.10

Data analysis will be performed using SAS 9.2 (SAS Institute Inc., USA) according to a pre-established statistical plan. The evaluation of effectiveness will adhere to the intention-to-treat principle. Quantitative data will be analyzed using methods such as ANOVA. Categorical data will be evaluated with chi-square tests and Fisher's exact test, while non-parametric rank sum tests and CMH chi-square tests will be used for ordinal data. The significance level will be set at *α* = 0.05, and a *P*-value below 0.05 will indicate a statistically significant difference. Descriptive statistics will summarize the baseline characteristics of the two groups. For continuous variables that are normally distributed or have an unknown distribution, *T*-tests or Mann–Whitney *U*-tests will be employed. To address missing data, appropriate imputation strategies will be used to minimize potential bias. This will involve multiple imputation techniques, allowing us to create several complete datasets by estimating missing values based on observed data trends. Proper handling of data is crucial for maintaining the precision, reliability, and traceability of clinical trial information, as stipulated by the Technical Guidelines for Clinical Trial Data Management (27) and the Good Clinical Practice standards (28).

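### Only unadjusted methods are named for the change in MBF; adjusting for the baseline MBF already measured would usually gain precision and should be stated as the primary analysis

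*Protocol article*

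**What the plan says.** Section 2.7.1 of the protocol article defines the primary endpoint: "The main endpoint is the change in myocardial blood flow (MBF), assessed through adenosine stress RTMPE, following a 12-week treatment period". Table 2 places RTMPE, the imaging that yields MBF, at baseline (weeks −2 to 0) and at week 12, so the schedule provides a baseline value without extra visits.

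Section 2.9 bases the sample size on mean change in each arm. From the literature, the "conventional treatment group increased by 0.52 ± 0.72 (dB/s) after 12 weeks", while with added TCM treatment "MBF variation increased by 0.97 ± 0.68 (dB/s) after 12 weeks". The result is 39 per group, raised to 49 for 20% dropout, 98 in total.

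Section 2.10 says that analysis will proceed "according to a pre-established statistical plan", which is not shown, and that effectiveness follows intention to treat. It then states "Quantitative data will be analyzed using methods such as ANOVA". Later, just after a sentence on summarizing baseline characteristics, it assigns t-tests or Mann–Whitney tests with the words "For continuous variables that are normally distributed or have an unknown distribution". Multiple imputation is planned for missing data. No covariate, regression model or ANCOVA is named anywhere in the article.

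**The concern.** Every method the article names for continuous data is an unadjusted group comparison, and the sample size rests on one as well. A change score uses the baseline, but in a fixed way: it subtracts it with a slope of 1. ANCOVA estimates that slope from the data. When the true slope is below 1, the change score subtracts too much. This adds noise, and an arm that starts higher by chance will tend to show a smaller change for reasons unrelated to treatment.

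The trial is small and single-centre, so some chance imbalance in baseline MBF is realistic. At stake are the width of the confidence interval for the primary effect, and power if dropout or the SD turns out worse than assumed.

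**Working it through.** **Inputs.** From section 2.9: changes of 0.52 ± 0.72 and 0.97 ± 0.68 dB/s, α = 0.05, power 0.80, 20% dropout. Sidedness is not stated. The baseline to week-12 correlation r and the ratio k of the week-12 SD to the baseline SD are not given either, so both are assumptions and are varied below.

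**1. The plan's own figure.**
- Difference δ = 0.97 − 0.52 = 0.45.
- Pooled SD = √[(0.72² + 0.68²)/2] = √0.4904 = 0.700.
- n per arm = 2 × [0.700 × (1.960 + 0.842)/0.45]² = 38.02, rounded up to 39. A one-sided test would give 30, so the plan used a two-sided test.
- Dropout: 39/0.80 = 48.75, rounded up to 49; total 98.
- Exact power from the noncentral t distribution (76 df): 0.800 at 39 per arm and 0.883 if all 49 per arm are evaluable.

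The stated 39, 49 and 98 reproduce with an unadjusted two-sided comparison of change scores.

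**2. ANCOVA with equal SDs at both visits (k = 1).** With common SD s, the change score has variance 2s²(1 − r) and the ANCOVA residual has variance s²(1 − r²). The ratio is (1 + r)/2. Holding the change SD at 0.700 and δ at 0.45, with one error df spent on the covariate (75 df at 39 per arm):

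| r | variance ratio | effective SD | power at 39 per arm | n per arm for 80% | n after 20% dropout |
|---|---|---|---|---|---|
| unadjusted | 1.00 | 0.700 | 0.800 | 39 | 49 |
| 0.3 | 0.65 | 0.565 | 0.935 | 26 | 33 |
| 0.5 | 0.75 | 0.606 | 0.899 | 30 | 38 |
| 0.7 | 0.85 | 0.646 | 0.860 | 34 | 43 |
| 0.8 | 0.90 | 0.664 | 0.840 | 36 | 45 |

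**3. ANCOVA with unequal SDs.** The ratio becomes k²(1 − r²)/(1 + k² − 2rk). At k = 1.25:
- r = 0.5: 1.5625 × 0.75/1.3125 = 0.89 (against 0.75 at k = 1).
- r = 0.7: 1.5625 × 0.51/0.8125 = 0.98 (against 0.85).
- r = 0.8: 1.5625 × 0.36/0.5625 = 1.00 (against 0.90), so no gain.

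The last case has a simple reason. The regression slope is rk = 0.8 × 1.25 = 1, which is the slope the change score already imposes.

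**4. Chance baseline imbalance (k = 1).** If the arms differ at baseline by one standard error, s√(2/39), the expected difference in change moves by (1 − r) × s√(2/39) in the opposite direction, where s = 0.700/√[2(1 − r)].
- r = 0.3: s = 0.592, standard error 0.134, shift 0.094 dB/s.
- r = 0.5: s = 0.700, standard error 0.159, shift 0.079 dB/s.
- r = 0.8: s = 1.107, standard error 0.251, shift 0.050 dB/s.

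Against the planned effect of 0.45, these are about 21%, 18% and 11%. They are shifts conditional on an observed imbalance; averaged over randomizations the shift is zero.

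**The case against.** The strongest reply is that the article does not say baseline MBF will be left out of the model. The phrase introducing ANOVA gives an example rather than a closed list, and the article defers to a statistical plan that is not shown, which is where covariates are commonly fixed. This stands: a reader might infer a commitment to an unadjusted primary model, but the text does not go that far. What remains is that the published methods and the published sample size both point to an unadjusted comparison.

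Three other stronger readings are tempting and also go too far.
- A reader might infer that chance imbalance is left uncorrected. It is not: the change score subtracts the baseline, and the fault when the slope is below 1 is over-correction.
- A reader might infer that the primary test will be picked between the t-test and Mann–Whitney after seeing the data. That sentence follows the one on baseline characteristics and may concern only those comparisons.
- A reader might infer that the trial has no margin in power. The 0.800 applies after the full 20% dropout; with less dropout power is higher, up to 0.883.

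It is also fair to object that the gain rests on an unknown r and on equal variances. MBF is expected to rise in both arms, so a larger SD at week 12 is plausible, and step 3 of the working shows that this can erase the gain.

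**Conclusion.** The point holds as one of efficiency, not validity. The unadjusted comparison of change is unbiased under randomization, agrees with the endpoint and the sample size, and has its stated 80% power at 39 evaluable per arm. ANCOVA on baseline MBF is generally the better use of data the trial already collects. Under equal variances it cuts the variance by 10% to 35% for r from 0.8 to 0.3, and raises power at 39 per arm to between 0.84 and 0.94. If r is high and the week-12 SD is larger, the gain may be negligible, as at r = 0.8 with an SD ratio of 1.25. Both r and the SD ratio are assumptions, since the article gives neither. The change is worth making, but the trial does not fail without it.

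**What to change.** State the primary analysis in section 2.10 as ANCOVA of week-12 MBF (or of its change; the treatment estimate is the same once baseline is in the model) on treatment group and baseline MBF. Fit it within the planned multiple imputation and report the adjusted mean difference with its 95% confidence interval. Keep any rank-based test as a sensitivity analysis only. Apply the same baseline adjustment to the Seattle Angina Questionnaire and TCM symptom scores, which Table 2 also schedules at baseline. If the statistical plan already specifies this, align section 2.10 with it.

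The cost is a sentence or two of text, settled before unblinding. It needs no added patients, visits or measurements, and the sample size of 98 can stand.
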